### FOLLOW-UP:

Patients will visit the outpatient department for physical examination (3 months) and X-rays (24 months). All measurement outcomes will be obtained at baseline, 3, 6, 9, 12, 18 and 24 months, online or by hardcopy if preferable. Patients will be examined by a well experienced clinician at each site. The anticipated enrolment period will be approximately one year with follow up.

We also plan to perform another long-term outcome measurement after 5 years.

Endpoint: the first results of the study will be evaluated after 1 year of follow up. The endpoint for the primary outcome of the study will be after 2 years of follow up. However, we plan a follow up moment at 60 months to see the progression of osteoarthritis, measured with the Kellgren Lawrence Grading Scale for Osteoarthritis.

Sample size calculation:

Sample size is based on a power of 90%, an alpha of 0.05, a standard deviation of 18 points and a non-inferiority threshold of 8 points on the IKDC 'Subjective Knee Form'.

We calculated that with 10% loss to follow-up after 24 months and 25% delayed APM in PT group, 160 patients are needed per group in this equivalence type RCT. This means a total of 320 patients will be included. Sample size is calculated for the intention-to-treat analysis.

Assigning patients to treatment groups:

After signing and dating the informed consent form, patients will be randomized. This will be done in a web-based system, using the ALEA software, stratified for each site and for 2 age subgroups:

Subgroup 1: 45-57 years of age

Subgroup 2: 58-70 years of age

Patients who are excluded from the study will get treatment at the discretion of the surgeon. Patients who prefer not to participate will be asked for their reasons. These reasons will be recorded.

Data Management:

Database management will be done using a web-based system.

Safety: the occurrence of adverse events and subsequent knee surgeries will be queried and recorded at follow-up visits.

[figure not shown]**Figure 1: Study Flowchart**

\* Total follow up time for primary outcome in delayed APM group remains 24 months

CRF s\* = surgery / CRF c\*=conservative, CRF d\*=delayed

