#### 6.4 Sample size calculation

Sample size is based on a power of 90%, an alpha of 0.05, a standard deviation of 18 points and a non-inferiority threshold of 8 points on the IKDC (a minimal clinical important change in IKDC is 8.8) (18).

We calculated that with 10% loss to follow-up after 24 months and 25% delayed APM in the PT group, 160 patients are needed per group in this non-inferiority RCT.

This corresponds to a total of 320 patients will be included.

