### Delayed surgery group:

Based on patients complaints, findings during physical examination and the level of pain, the physician and/or surgeon and patient will decide in agreement that conservative treatment has failed and choose for delayed arthroscopic partial meniscectomy. This can be done no earlier than 3 months after randomization during the entire follow up time of the study. Prior to the delayed APM patients will be asked to answer an extra questionnaire as endpoint of PT. Patients in this group will be analyzed in the PT group according to the Intention-to-treat principle.

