In all models, missing data (intermittent/drop-out) will be analyzed on being missing completely at random (MCAR) or not (missing at random [MAR]). If not, each model will either be appropriately corrected or missings will be appropriately imputed (to be determined; e.g. last observation carries forward or multiple imputation). In the intention-to-treat analysis we already anticipate a 25% dropout which is non-ignorable (intervention related). Therefore, these data will be analyzed using a weighted GEE analysis. We will consult a statistician for all GEE analysis.

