#### Patient outcome analysis:

Effect measures in the economic evaluation are physical function, pain intensity and general health. Quality-adjusted life-years (QALYs) based on the Dutch tariff for the EuroQol will also be measured (22;29).

The analysis will be done according to the intention-to-treat principle. Missing cost and effect data will be imputed using multiple imputation according to the MICE algorithm developed by Van Buuren (30).

Full cost-effectiveness and cost-utility analyses will be performed. Incremental cost-effectiveness ratios (ICERs) will be calculated by dividing the difference in mean total costs between the treatment groups by the difference in mean effects.

Bias-corrected and accelerated bootstrapping with 5000 replications will be used to estimate 95% confidence intervals around cost differences and the uncertainty surrounding the ICERs. Rubin's rules will be used to pool the results from the different multiply imputed datasets. Uncertainty surrounding the ICERs will be graphically presented on cost-effectiveness planes.

Cost-effectiveness acceptability curves will also be estimated using the net benefit framework (31). Cost-effectiveness acceptability curves show the probability that APM is cost-effective compared with PT for a range of different ceiling ratios thereby showing decision uncertainty (32).

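### Section 10 plans for a 25% non-ignorable dropout in the ITT analysis, which conflicts with keeping delayed-APM patients in the PT arm and with the stated 10% loss, and weighted GEE cannot repair it

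*Protocol*

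**What the plan says.** Protocol Section 10 (Statistical analysis, missing data) states: "In the intention-to-treat analysis we already anticipate a 25% dropout which is non-ignorable (intervention related". It concludes that "these data will be analyzed using a weighted GEE analysis". The sentence before leaves the handling of other missing data open: "to be determined; e.g. last observation carries forward or multiple imputation", depending on whether the data prove to be missing completely at random.

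Other parts of the protocol bear on the same patients:

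- Section 7, Delayed surgery group: "Patients in this group will be analyzed in the PT group according to the Intention-to-treat principle".
- Section 5, footnote to Figure 1: "Total follow up time for primary outcome in delayed APM group remains 24 months".
- Section 6.4: the sample size allows for "10% loss to follow-up after 24 months and 25% delayed APM in the PT group". Section 5 repeats these rates and says that the number is for the intention-to-treat analysis.
- Section 10, Patient outcome analysis (economic evaluation): "Missing cost and effect data will be imputed using multiple imputation". The effect measures there include physical function.

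**The concern.** A patient who has delayed APM and goes on answering questionnaires is a crossover, not a dropout. Under Section 7 and the Figure 1 footnote, that patient's 24-month IKDC is planned, observed PT-arm data. Section 10 appears to put the same patients under a missing-data rule. Weighting can act on the 25% only if their scores count as missing. If that is the intention, the analysis labelled ITT would estimate something like PT without delayed surgery, which is a different question from the effect of a policy of PT first with surgery available.

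There is a second fault on any reading. Standard inverse-probability-weighted GEE is valid when missingness is explained by observed data (MAR). Section 10 chooses it because the dropout is non-ignorable, which is the case it does not cover.

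At stake is the primary non-inferiority conclusion. About a quarter of one arm could be kept or set aside depending on which section the analyst follows, in an open-label trial.

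**Working it through.** **Inputs.** Section 6.4 gives "a power of 90%, an alpha of 0.05, a standard deviation of 18 points and a non-inferiority threshold of 8 points", with 10% loss, 25% delayed APM and 160 per group. Section 10 uses two-tailed 0.05, read here as one-sided 0.025 for non-inferiority. A true difference of 0 is assumed, from the hypothesis of equal improvement.

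**Step 1: reproduce the 160.** Evaluable patients per arm: n = 2 × [SD × (z₀.₉₇₅ + z₀.₉₀) / margin]² = 2 × [18 × (1.960 + 1.282) / 8]² ≈ 106.4, so 107.

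| Inflation | Per arm |
|---|---|
| 10% loss only: 107/0.90 | 119 |
| 25% only: 107/0.75 | 143 |
| Both, added: 107/0.65 | 165 |
| Both, multiplied: 107/(0.90 × 0.75) | 159 |

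The last row matches 160. Section 5 also calls the trial an equivalence type. Two one-sided tests at 0.05 each need 110 evaluable, giving 110/(0.90 × 0.75) = 163 with both allowances and 110/0.90 = 123 with loss only. The variants that come close to 160 therefore count the delayed-APM 25% as lost, and do so in both arms although delayed APM arises only in the PT arm. This supports reading the 25% in Section 10 as the same patients.

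**Step 2: what follows if crossovers stay in.** Only the 10% loss needs inflation, so 119 per arm suffice. At 160 per arm, 160 × 0.90 = 144 are evaluable. The standard error is 18 × √(2/144) = 2.121, and power = Φ(8/2.121 − 1.960) = Φ(1.811) = 96.5%. With 108 per arm (160 × 0.675) it is 90.4%. Neither figure allows for a change in effect or SD caused by crossover.

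**Step 3: size of the departure from ITT under plain removal.** Let f be the crossover share and D the amount by which crossovers' 24-month change, after surgery, lies below that of other PT patients. Removing crossovers shifts the PT mean by f × D. D is not in the protocol, so a range is shown.

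| f | D = 5 | D = 10 | D = 15 | D = 20 |
|---|---|---|---|---|
| 0.25 (Section 6.4) | +1.25 | +2.5 | +3.75 | +5.0 |
| 1/3 (Section 8.1.2, hypothesis 9) | +1.7 | +3.3 | +5.0 | +6.7 |

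At f = 0.25 this is 16% to 62.5% of the 8-point margin. If delayed APM brings crossovers level with the others or above them (D ≤ 0), the shift is zero or against PT.

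**Step 4: what weighting does.** A simulation of 2,000,000 PT patients assumed SD 18, a correlation of 0.6 between the interim and the untreated 24-month score, 25% crossover driven by poor scores, and a gain of 0, 5, 10 or 15 points from delayed APM. Entries are the error in the PT mean relative to ITT; positive favours PT.

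| Crossover depends on | Method | Gain 0 | 5 | 10 | 15 |
|---|---|---|---|---|---|
| Observed interim score | Plain removal | +2.6 | +1.4 | +0.1 | −1.1 |
| Observed interim score | Weighted on interim score | 0.0 | −1.3 | −2.5 | −3.7 |
| Unobserved 24-month outcome | Plain removal | +4.4 | +3.1 | +1.9 | +0.6 |
| Unobserved 24-month outcome | Weighted on interim score | +3.0 | +1.7 | +0.5 | −0.8 |

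The last two rows are the non-ignorable case that Section 10 itself asserts. There, weighting removes only part of the selection. In the first two rows it removes the selection but, once surgery helps, it misses the ITT mean because the surgical gain is left out.

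**The case against.** **The 25% is never identified.** Section 10 does not mention delayed APM in the sentence at issue. Section 8.4 (Withdrawal of individual subjects) uses drop-out for people who leave the study, while Section 10 elsewhere calls the delayed-APM patients crossovers and treatment failures. On that vocabulary the 25% could be an attrition figure. This stands as a caution: the delayed-APM reading is a strong inference, not text. It does not rescue the sentence, because 25% attrition contradicts the 10% in Sections 5 and 6.4.

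**Nothing says that post-APM scores are discarded.** This also stands. Setting them aside is what a missing-data method would imply, but no passage orders it, and Section 7 states the proper ITT rule. One could say that Section 7 governs. But Section 10 is where the analyst looks for the method, and the two do not agree.

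**The bias has no fixed sign.** A reader might infer that the plan removes PT failures and so biases towards non-inferiority, or might attach an inflated false-positive rate to it. The documents do not support either. Weighting is not plain deletion; the direction depends on what drives crossover and on the gain from delayed surgery; and such an error rate would describe PT without surgery, not the ITT comparison.

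**LOCF and per-protocol.** LOCF is only an undecided example for missing data in general and is not tied to the 25%; a final choice may properly sit in a SAP. In the simulation above, carrying the pre-surgery score forward shifted the PT mean by between −5.0 and +1.3 points, mostly against PT. Nor can one say that the per-protocol analysis shares the problem, because the protocol does not define that set as excluding crossovers.

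**Conclusion.** Wrong as written, on either reading. If the 25% means delayed-APM patients, as is likely, Section 10 contradicts Section 7 and the Figure 1 footnote and would change what the primary analysis estimates. If it means true attrition, it contradicts the stated 10%. In both cases standard weighted GEE does not answer the problem for which it was chosen.

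The possible error is material. Under the assumed inputs, weighting puts the PT mean between 3.7 points too low and 3.0 points too high relative to ITT, against a margin of 8. These figures rest on the assumed correlation, crossover model and surgical gains; they show the scale and the lack of a fixed direction, and do not predict the trial's bias. The contradiction and the MAR point need no such assumptions.

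**What to change.** Delete the two sentences on the 25% dropout and weighted GEE, and replace them with wording such as:

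> All IKDC scores observed up to 24 months enter the intention-to-treat analysis in the randomised arm, including scores obtained after delayed APM. Missing-data methods apply only to scores that were not obtained.

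For truly missing scores, name one primary method valid under MAR in place of LOCF. The multiple imputation already planned for the economic evaluation would do, and would keep the clinical and economic analyses consistent on the IKDC. Add a delta-adjusted sensitivity analysis that shifts imputed scores and reports whether the conclusion against the 8-point margin changes. If 25% true attrition was meant, correct whichever of the 25% and the 10% is wrong.

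Reconcile the sample-size wording in Sections 5 and 6.4. With crossovers kept in, only the 10% loss needs inflation (119 per arm), so 160 per arm has room to spare at a true difference of 0. State that the figure allows for no change in effect or SD from crossover, or justify the extra allowance on other grounds.

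The cost is wording and a little more analysis. The 24-month IKDC is already scheduled for every patient, so no new data are needed.

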### Cost-effectiveness analysis

General considerations:

The economic evaluation will be conducted from a societal perspective. The aim of the economic evaluation is to measure, value and analyze total costs of patients in both groups and to relate the difference in costs between the two treatment groups to the difference in clinical effects. Both a cost-effectiveness and cost-utility analysis will be performed. The time horizon of the economic evaluation is 24 months, so discounting will be used. Sensitivity

analysis will be performed to assess the robustness of the results using different assumptions regarding costs and effects.

#### Cost-analysis:

Costs will be measured using web-based questionnaires based on the TiC-P at baseline and after 3, 6, 9, 12, 18 and 24 months of follow-up (23). Direct costs include costs of APM surgery and costs of PT, but also other healthcare utilization for knee problems such as GP care, costs of visits to other primary care providers, ambulatory and inpatient hospital care, medication and home care. Indirect costs include absenteeism from paid and unpaid work and presenteeism. The friction cost approach will be used in the primary analysis to estimate indirect costs (27). For the valuation of healthcare utilization standard prices published in the Dutch costing guidelines will be used (28). Medication use will be valued using prices of the Royal Dutch Society for Pharmacy.

#### Patient outcome analysis:

Effect measures in the economic evaluation are physical function, pain intensity and general health. Quality-adjusted life-years (QALYs) based on the Dutch tariff for the EuroQol will also be measured (22;29).

The analysis will be done according to the intention-to-treat principle. Missing cost and effect data will be imputed using multiple imputation according to the MICE algorithm developed by Van Buuren (30).

Full cost-effectiveness and cost-utility analyses will be performed. Incremental cost-effectiveness ratios (ICERs) will be calculated by dividing the difference in mean total costs between the treatment groups by the difference in mean effects.

Bias-corrected and accelerated bootstrapping with 5000 replications will be used to estimate 95% confidence intervals around cost differences and the uncertainty surrounding the ICERs. Rubin's rules will be used to pool the results from the different multiply imputed datasets. Uncertainty surrounding the ICERs will be graphically presented on cost-effectiveness planes.

Cost-effectiveness acceptability curves will also be estimated using the net benefit framework (31). Cost-effectiveness acceptability curves show the probability that APM is cost-effective compared with PT for a range of different ceiling ratios thereby showing decision uncertainty (32).

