## 8.2 Randomization, blinding and treatment allocation

We will include 320 patients between 45 and 70 years with MRI-confirmed symptomatic, non-obstructive meniscal tears. Randomization will be performed in a 1:1 ratio by a computerized software program (TENALEA Clinical Trial Data Management System) using random blocks with maximum block size 6, stratified for center and age group.

- a. Open study (no blinding)
- b. Number of randomization arms : 2
- c. Specification of the arms : APM vs PT
- d. Weight of the arms : 1:1
  - Type of randomization : Random block, max block size 6
- e. Strata and categories:
  - Age : (45-57) and (57-70)
  - Centers : a maximum of 10
- f. No deletion or replacement of participants (unless false randomization due to clear technical issues)

At time of presentation at the outpatient department, people suspected for a meniscal injury will be informed about the study with an information letter. When they return to the outpatient department for the results of the MRI, they will be asked for participation in the study. After informed consent is signed, the local physician/surgeon contacts the randomization website and submits a patient's details and treatment center to the online TENALEA data management program and receives treatment allocation when submitting this information to the website. All data management will be recorded online, unless patients are unable or unwilling to complete the questionnaires online.

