- g) **EQ-5D5L - Quality of Life:** The generic effects on quality of life will be assessed with the Euroqol EQ-5D5L (22). This widely used quality-of-life instrument includes five dimensions

of health related quality of life, namely mobility, self-care, daily activities, pain/discomfort, and depression/anxiety. These five dimensions will be combined into a health state.

- h) *Costs and EQ-5D5L - Cost-utility*: To establish the costs, relevant cost items are identified, after which these costs are measured and values are placed on the cost items. These relevant cost items are: the total surgery time and the costs surgery versus the costs of physical therapy.  
Utility values will be calculated for the health states of the EQ-5D5L, using preferences elicited from a general Dutch population. The utility values will be used to compute quality-adjusted life-years (QALY-EQ-5L5D) by means of the area under the curve method.
- i) *TiC-P part II (Trimbos/iMTA questionnaire for Costs associated with psychiatric illness)* measures costs and consequences of productivity losses (indirect costs). Part II of the TiC-P is a shortened version of the Health and Labour questionnaire and is appropriate for the measurement of productivity losses in both physical and psychiatric conditions. It has 4 modules: absenteeism from paid work, production losses without absenteeism from paid work, unpaid work and nuisance in paid and unpaid work and contains of 11 questions (23). In this modified version of the TiC-P, prepared by prof. [name] of the VU University Amsterdam, we will also measure the use of healthcare services.
- j) *PSC (patient specific complaints)* is a patient reported questionnaire, in which patients report on specific activities and movements in which they experience symptoms. It contains of 28 normal daily activities and movements. The patient selects 3 activities or movements in which they experience symptoms and they prefer to improve in the next months. They are then asked to fill in a visual analogue scale (of 10 cm) in which report the amount of complaints they experience (24).

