## 10. STATISTICAL ANALYSIS

Data-analysis and presentation:

To investigate the effect of surgery, we will use generalized estimating equations (GEE) for longitudinal analysis in SPSS 18 on an intention-to-treat and per-protocol basis, as well as sub-group analysis of the cross-over patients. This method takes into account the dependency of observations within a patient, and the fact that not all patients may be assessed at each time point (missing data). In the primary GEE model, the outcome variable studied (e.g. physical function on the IKDC) will be analyzed as a dependent variable, using treatment allocation (1, intervention; 0, control) and time as a key independent variables. In the secondary GEE model, the outcome variables studied (e.g. general health on the RAND36, quality of life on the EQ5D-5L, level of activity on the TAS, knee pain on the question 10 of IKDC, the correlation between a patient's expectation and satisfaction, productivity losses on TiC-P, muscle strength, range of motion, squatting and adverse events) will be analyzed in a similar way. To evaluate whether the two groups differed in change over time the interaction term of group and time (group X time) will be assessed. Time will be included as a dummy variable (reference = baseline T0), and four interaction terms will be analyzed (T1Xgroup; T2x group; T3x group, T4x group). All models will be corrected for center of inclusion and age group. In additional analysis, we will investigate the possible confounding effect (defined as more than 10% change in the parameter estimate for groupXtime) of 5 variables (body mass index, gender, profession, ASA-classification, the affected meniscus, the type of tear and the stadium of OA according to the Kellgren Lawrence Grading Scale for Osteoarthritis).

At the following time points following the treatment (T2, T3, T5 and T7) we will describe the incidence of revisions (intervention group) or treatment failures (=delayed APM, control group) using descriptives. After two years (T7) we will compare the incidence of development or progression of OA between groups using a chi-squared test (or Fisher's Exact as appropriate). For all analysis, a two-tailed value of  $p < 0.05$  is considered to be significant.

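### As ordinarily read, the cost-utility comparison does not adjust for baseline utility, baseline costs or the randomisation strata: it is unbiased, but less precise than the collected data allow

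*Protocol*

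**What the plan says.** - **QALY construction** (Protocol, Section 8.3, item h): "The utility values will be used to compute quality-adjusted life-years (QALY-EQ-5L5D) by means of the area under the curve method".
- **Measurement times** (Section 5, Follow-up): "All measurement outcomes will be obtained at baseline, 3, 6, 9, 12, 18 and 24 months". Table 1 lists EQ-5D-5L at all seven of these times, so the curve starts at baseline.
- **Costs** (Section 10, Cost-analysis): "Costs will be measured using web-based questionnaires based on the TiC-P at baseline and after 3, 6, 9, 12, 18 and 24 months". A baseline TiC-P value is therefore available too.
- **Estimator** (Section 10, Patient outcome analysis): the ICER is "calculated by dividing the difference in mean total costs between the treatment groups by the difference in mean effects". The same subsection specifies multiple imputation, a bias-corrected and accelerated bootstrap with 5000 replications, and pooling by Rubin's rules. It names no covariate.
- **Clinical models** (Section 10, opening paragraphs): "All models will be corrected for center of inclusion and age group". This sentence belongs to the account of the GEE models, and the economic subsections do not refer back to it.
- **Strata** (Section 8.2): randomisation is done "using random blocks with maximum block size 6, stratified for center and age group".

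**The concern.** A patient's utility at entry usually predicts later utilities, and it is also the first point of that patient's area under the curve. If the arms differ by chance at baseline, an unadjusted comparison passes part of that difference into the QALY contrast. In the GEE, the group-by-time terms take baseline as reference, so the baseline difference is subtracted. The economic section describes no comparable step.

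Cost-effectiveness is one of the two aims in Section 4. Hypothesis 4 in Section 8.1.2 expects equal improvement in quality of life measured in QALYs, so the true QALY difference is expected to be small. A modest shift can then change the sign of the observed difference, and with it the quadrant of the cost-effectiveness plane and the shape of the acceptability curve. The results are meant for reimbursement policy makers (Section 12.5).

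**Working it through.** **The plan's own figure.** The only design figure is 160 per group for the IKDC, from "Sample size is based on a power of 90%, an alpha of 0.05, a standard deviation of 18 points" and a margin of 8 points. With one-sided alpha 0.025, n = 2 × [18 × (1.960 + 1.282) / 8]² gives 107 per group. Allowing for 10% loss and 25% delayed surgery, 107 / (0.90 × 0.75) = 159, in line with 160. This says nothing about QALY precision. The Protocol states no QALY SD, EQ-5D SD or EQ-5D correlation, so everything below rests on assumed values shown as ranges.

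**Step 1: weights.** The trapezoid rule over 0, 3, 6, 9, 12, 18 and 24 months gives 0.125, 0.25, 0.25, 0.25, 0.375, 0.5 and 0.25 years, which sum to 2.0. Baseline has 0.125 / 2.0 = 6.25% of the weight. The discounting announced in Section 10 is ignored here; its effect over two years is small.

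**Step 2: variance removed by adjustment.** Assume equal variances at all visits and an exchangeable correlation ρ. In units of the utility variance:
- Cov(QALY, baseline) = 0.125 + 1.875ρ
- Var(QALY) = 4ρ + 0.65625(1 − ρ), where 0.65625 is the sum of squared weights
- Share removed: r² = Cov² / Var. The unadjusted interval is 1/√(1 − r²) times as wide as the adjusted one.

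| ρ | Cov | Var | r² | Interval ratio |
|---|---|---|---|---|
| 0.3 | 0.688 | 1.659 | 0.29 | 1.18 |
| 0.5 | 1.063 | 2.328 | 0.49 | 1.39 |
| 0.7 | 1.438 | 2.997 | 0.69 | 1.79 |

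**Step 3: a less favourable structure.** Let follow-up visits correlate 0.7 with each other, and baseline correlate 0.2, 0.3, 0.4, 0.5 or 0.6 with each of them. Then r² is 9%, 17%, 27%, 39% or 53%. At the low end the interval ratio is 1/√(1 − 0.09) = 1.05. Over assumed baseline-to-follow-up correlations of 0.2 to 0.7 and both structures, the range is about 9% to 69%. It is not a bound: an exchangeable correlation of 0.8 would give 79%.

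**Step 4: carry-over of a chance imbalance.** The covariance in Step 2 is also the slope. A baseline difference d between arms shifts the expected QALY difference by (0.125 + 1.875ρ) × d, which is 0.69d, 1.06d or 1.44d at ρ = 0.3, 0.5 or 0.7.

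Take an assumed utility SD of 0.20 and 160 per arm:
- The SE of the baseline difference is 0.20 × √(2/160) = 0.022, so an imbalance of 1.96 SE is 0.044.
- This moves the two-year QALY difference by 0.030, 0.047 or 0.063 at ρ = 0.3, 0.5 or 0.7.
- Only 0.125 × 0.044 = 0.0055 of that comes from baseline's own place in the curve.
- At ρ = 0.5, an SD of 0.15 to 0.25 gives 0.035 to 0.058.
- With 160 × 0.90 = 144 per arm and SD 0.20, the three shifts are 0.032, 0.049 and 0.066.

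**The case against.** The strongest reply is that the ICER sentence is only the general definition of the ratio. It does not call the means raw or unadjusted, regression-adjusted means would satisfy it, and an analysis plan not shown here may name covariates. A reader might infer that the Protocol prescribes an unadjusted analysis; its words do not go that far. What remains is that the subsection fixes the imputation algorithm, the bootstrap type, the number of replications and the pooling rule, and gives the estimator as a plain difference of means. The ordinary reading is unadjusted, and an analyst could choose either version after seeing the data.

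A reader might also infer that the QALY difference or the ICER is biased. It is not. Under 1:1 randomisation the unadjusted difference is correct on average, and chance imbalance is already part of the variability that the bootstrap interval, plane and acceptability curve show. The harm is lost efficiency, plus an estimate that is off in the particular trial where an imbalance is observed.

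It is tempting to say that about half the precision is lost. That is one assumed case, an exchangeable correlation of 0.5, and no figure in the Protocol supports it over the others. Half the variance also means an interval about 1.4 times as wide, not twice as wide.

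Finally, EQ-5D-5L and TiC-P productivity losses are among the GEE outcomes, with strata correction and baseline as reference, and Section 10 promises sensitivity analyses on cost and effect assumptions. Both help interpretation. Neither commits the plan to adjusted QALY or cost differences in the ICER.

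**Conclusion.** The point holds as an available gain in precision, not as an error of validity. On its ordinary reading, the economic comparison leaves baseline utility, baseline costs, centre and age group unused although all are collected. Under assumed baseline-to-follow-up correlations of 0.2 to 0.7, adjusting for baseline utility would remove roughly 9% to 69% of the QALY variance. The unadjusted QALY difference moves by about 0.7 to 1.4 per unit of baseline utility imbalance at exchangeable correlations of 0.3 to 0.7, almost all of it through correlation with follow-up and not through baseline's share of the curve.

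These sizes depend on the assumed correlations, equal variances across visits and, for the absolute shifts, an assumed SD. The gain from adjusting costs for baseline TiC-P, or either outcome for the strata, cannot be sized from the Protocol. No conversion to euros is given, because the Protocol states no value per QALY.

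**What to change.** In Section 10, Patient outcome analysis, add wording such as:

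*Incremental QALYs will be estimated by regression of the 24-month QALY on treatment allocation, baseline EQ-5D-5L utility, centre and age group. Incremental costs will be estimated by regression of total costs on treatment allocation, baseline TiC-P costs, centre and age group. Both regressions will be fitted within each imputed dataset and bootstrap replicate, and the adjusted differences will be used for the ICER, the cost-effectiveness plane and the acceptability curve. The unadjusted differences will be reported as a sensitivity analysis.*

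Regression is preferable to subtracting baseline. Taking two years at baseline utility off each QALY would, at ρ = 0.5, turn the slope of 1.06 into 1.06 − 2 = −0.94, which replaces one carry-over with another of similar size and opposite sign.

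The cost is a few lines of text and two regressions inside a bootstrap and imputation loop that is already planned. The baseline values should also be in the imputation model. Patients, visits, questionnaires and sample size do not change.
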